### Secondary outcomes

***EPAO-SR tool***: This instrument will also capture: a) change in the characteristics of the providers (educators and managers) including skills, self-efficacy, and commitment to change facility practices to implement the AP standard; and b) changes in organizational processes implemented by managers including actions to prioritize AP (such as establishing a champion, modifying policies, setting goals and routines, routinizing processes, monitoring, etc.); and c) changes in the environment such as modifying the indoor or outdoor environment to support AP and FMS.

### Randomization

A computer-generated (www.sealedenvelope.com) randomization schedule will be used to allocate participants in blocks of two, four, six, or eight participants with a randomization ratio of 1:1. The allocation schedule will be concealed in the randomization module of REDCap and only assigned after informed consent and baseline assessments have been completed. Research team members and participants are blinded to allocation at baseline. They will not enter or modify the allocation schedule, as it will be entirely computer-generated. After randomization, participants and research team members will not be blinded to the allocation conditions because participants will know whether they receive the ATP+ intervention immediately or in 3 months, and team members will be tasked with providing intervention group participants access to the intervention. Allocation assignment will be concealed from the researchers at the analysis stage.

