### Primary outcomes

***Change in AP and FMS practices***: Child engagement in AP and FMS activities (i.e., time spent in AP, time spent in FMS, number of FMS activities, time spent outdoors, number of outdoor sessions, and an index on the number of best practices facility adheres to) will be measured with field observation and self-report. For field observations, we will use a modified version of the Environment and Policy Assessment and Observation (EPAO) tool [27], which captures type of AP and FMS (locomotor, agility, and/or object/control) activity, duration, location (indoor or outdoor), and intensity of movement. The field observations will initially be completed independently by two trained members of the research team and involve one observer once high intra-observer consistency is obtained. The observations will take place for eight hours of the ECEC centre’s operational times (8:30am-4:30 pm), to capture the activities when most children are present at the facility. The self-report evaluation will be based on questions from the Early Years Survey and the EPAO as a Self-Report instrument (EPAO-SR), adapted to specifically assess the practices targeted by the AP standards in BC, such as providing a minimum of 60 minutes outdoor AP time per day, at least 120 minutes of AP per day, and the use of both facilitated and unfacilitated AP activities that cover FMS [27].

***Change in FMS***: Child FMS will be assessed with the Test of Gross Motor Development version 3 (TGMD-3), a validated, norm-referenced tool for assessing 13 gross motor skills in both locomotor and object control categories [28]. A modified TGMD-3 protocol is commonly used in early childhood movement skill interventions [29]. In this study, we will evaluate six skills: gallop, hop, horizontal jump, two-hand catch, kick a stationary ball, and overhand throw. A composite score will be computed for locomotor and ball skills with a gross motor composite score computed for the analyses. The TGMD-3 performances will be videoed by the research team and scored at a later date. Two members of the research team will independently score the children on the TGMD-3 criteria and discrepancies will be discussed with a third reviewer.

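### Follow-up field observers are left unblinded for a reason that applies only to whoever releases the app, so the judgement-based parts of the observed practice outcome carry observer bias that could be reduced

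*Protocol article*

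**What the plan says.** The Randomization section of the protocol article sets a general rule for the period after allocation: "After randomization, participants and research team members will not be blinded to the allocation conditions". It gives two reasons. The first concerns centres and their staff: "participants will know whether they receive the ATP+ intervention immediately or in 3 months". The second concerns the team: "team members will be tasked with providing intervention group participants access to the intervention". The same section says that allocation is unknown to everyone at baseline, and that it is hidden again from the researchers when the data are analysed.

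Under Primary outcomes, change in active play (AP) and fundamental movement skill (FMS) practices "will be measured with field observation and self-report". Trained research team members carry out the observation over an eight-hour day with a modified EPAO tool. Two observers work independently at first, and later visits "involve one observer once high intra-observer consistency is obtained". The tool records the type of activity and its "duration, location (indoor or outdoor), and intensity of movement". The child motor outcome is handled differently: "The TGMD-3 performances will be videoed by the research team and scored at a later date", by two team members working independently, with a third reviewer for discrepancies.

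According to Data collection, follow-up takes place about three months after baseline. The Development of ATP+ section says that the content reaches staff through the Pathverse app.

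**The concern.** The rule unblinds the whole team, but the reason given for the team reaches only the people who switch on app access. Nothing in the article requires the person observing a centre at follow-up to be one of them.

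This matters because the field observation feeds a primary outcome and its records are made live. The article describes filming for the TGMD-3 only, so an observer's decision that a borderline episode counted as an FMS activity, or was vigorous enough, cannot be re-scored later. Self-report cannot be masked, since centres know when they receive the programme. Observation is thus the one source for the practice outcome that could be at least partly shielded from knowledge of the arm, and the rule as written gives that up.

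**Working it through.** The plan states no figure for this point, so the check sets the relevant statements side by side.

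1. **Who knows the arm at follow-up.** The Randomization section names participants and research team members as unblinded and makes no exception for outcome assessors. No other section makes one.

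2. **Why the team knows.** Of the two reasons given, one is about participants. The other is the granting of access, which takes place through an app. It explains why some team members must know the arm, but not why observers must.

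3. **Who makes the observations.** Research team members do, with one observer once consistency is judged high. Consistency does not reveal error that differs by arm: an observer can be perfectly repeatable and still lean the same way in every intervention centre.

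4. **What the existing safeguards cover.**
   - Blinding at baseline protects the baseline record only. The outcome is change, so the follow-up record is equally part of it.
   - Concealment at analysis begins after the observer's judgements have been recorded.

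5. **Which components are exposed.**
   - Judgement-based: type of activity, classification as FMS, intensity, and duration in so far as it depends on when an episode is taken to start and stop.
   - Little room for judgement: indoor or outdoor location, time outdoors, number of outdoor sessions.
   - Not assessed live: the TGMD-3, which is scored from video. The article does not say separately whether the scorers know the arm. The general rule covers them as team members, and it is unclear whether concealment at the analysis stage reaches scoring.

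6. **Size.** The documents give no observer error, no standard deviation and no control mean for observed minutes, so the bias cannot be calculated. What can be shown is how a test reacts to an assumed bias. Take a two-sided test at alpha 0.05 with 80% power for its planned effect (the values in the Sample size calculation; two-sidedness is assumed). The planned effect then lies 1.96 + 0.84 = 2.80 standard errors from zero. If the true effect is zero and observers add a differential error equal to a fraction f of the planned effect, the rejection rate is 1 − Φ(1.96 − 2.80f) + Φ(−1.96 − 2.80f):

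| Assumed f | Rejection rate |
|---|---|
| 0 | 5% |
| 0.10 | 5.9% |
| 0.25 | 10.8% |
| 0.50 | 28.8% |

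The values of f are assumptions with no support in the documents. The table also supposes that the observed measure is powered as the sample size section describes, but that section counts educators and does not say that its AP minutes are observed ones. It shows sensitivity and is not an estimate.

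**The case against.** The choice is disclosed and nothing in the article contradicts it. An observer who spends eight hours among staff who know their arm may well learn it, and ATP+ asks centres to revise schedules, appoint champions and build new installations, some of which will be visible. The tool is structured, the observers are trained and the early visits are double-observed. A procedural manual that is not shown may assign roles more finely. All of this stands, and it limits how much masking can achieve. It does not supply a reason to tell observers the arm in advance.

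Several stronger readings are tempting and are not supported:

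- *That the same individuals release access and observe.* The article does not say so. It unblinds the team as a group.
- *That the TGMD-3 is assessed live by unblinded staff.* It is filmed and scored later by two people. The article does not describe how staff demonstrate or prompt on the day, so bias by that route is speculation. Only the masking of the video scorers is a fair question.
- *That the whole observed outcome is compromised.* Outdoor time, session counts and location leave little to interpret.
- *That the bias can be set against the target effect.* One could take 15% of 120 minutes, which is 18 minutes, and compare a few misclassified minutes with it. But 120 minutes is a minimum in the practice standard and not a control mean, any episode length would be invented, and the 15% target may not refer to observed minutes.
- *That a positive result would be uninterpretable.* The direction of any bias is not documented, and the video-scored child outcome offers partial corroboration.

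**Conclusion.** The point holds in a limited form. The unblinding rule is wider than its stated reason, and it exposes the judgement-based components of the observed practice outcome at follow-up to observer bias that could be reduced, though not eliminated. Its size and direction cannot be established from the documents. The conclusion rests on reading the Randomization rule as covering follow-up observers, which its wording does without exception. It also assumes that at least some existing team members need not handle app access; the article mentions research teams at two universities but gives no staffing numbers. This is a low-cost improvement to the conduct of the trial and does not invalidate the design.

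**What to change.** In the Randomization section:

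- Limit knowledge of allocation after randomisation to the existing staff who release Pathverse access, enforced through REDCap user rights on the randomisation module.
- State that the remaining follow-up EPAO observations are done by existing team members who do not hold that role and have not been told the arm. Apply the same to the TGMD-3 video scorers.
- Ask centre staff not to disclose their arm to visiting observers.
- Add an item to the observation form in which the observer records whether, and when, the arm became known.

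In reporting, give the extent of unmasking by arm and keep every observation in the intention-to-treat analysis. Do not add an analysis restricted to masked observations. Unmasking happens after randomisation and is likelier in centres that have made visible changes, so the restriction would tend to drop the intervention centres that implemented most and would distort the comparison.

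The cost is a division of roles, a permission setting and one form item, with no new visits, outcomes or sample. The drawbacks are that masking will be partial and rostering less flexible. Data collection began in November 2023, so follow-up visits already completed can only be reported as unmasked.

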### Data confidentiality and anonymity

All data will be entered into REDCap hosted at the BCCHRI. REDCap is a secure, online software system created to facilitate data collection for research projects. It offers a user-friendly interface for validated data entry, comprehensive audit trails for monitoring data changes and exports, automated export features for easy data transfer to popular statistical programs, and methods for integrating and sharing data with external sources [30,31]. To protect participant anonymity, a unique identification number is given to each participant and names are stored in a different project. Participant confidentiality and the confidentiality of the data will be protected by having no participant or ECEC centre names on any of the data. Electronic files will be stored using a unique identification number on a secure network drive at the University of BC which will only be accessible to the investigators and research staff. Operating procedures will be documented in a procedural manual to standardize the administration of data collection methods, tracking procedures, and data entry methods into REDCap. Any adverse events will be reported to the University of BC Behavioural Research Ethics Board, and any changes to this protocol will be made to the clinical trials registry.

### Development of ATP+

ATP+ was developed by experts in the field of physical activity and AP for children in early childhood. The information in ATP+ builds on information from the Appetite to Play initiative. Appetite to Play was created as part of the Active People, Active Places strategy from the Government of BC to increase physical activity rates in a number of key focus areas from 2015–2025 [32]. Appetite to Play is a capacity-building intervention that utilizes implementation strategies, like providing accredited training and resources on physical and food literacy to early childhood educators, with the aim of enhancing children’s physical activity and nutritional habits [22,23]. It features an interactive website that offers users access to a wealth of resources, including physical activity suggestions and activities, knowledge translation articles and self-assessment and planning tools (*appetitetoplay.com*). Appetite to Play increased knowledge and confidence around AP [22] and implementation of the AP Standard increased the amount of time spent in outdoor play [20]. Barriers identified by educators were primarily less changeable characteristics of the setting such as the physical space, equipment and the attitudes and behaviours of other staff [24]. However, managers of these settings acknowledged that they had the ability to change some of these characteristics [24], which informed the development of ATP+ .

ATP+ involves training and resources in the application of facility-level implementation strategies such as integrating AP and FMS into scheduling, curriculum planning and creating a supportive environment for AP in ECEC facilities. ATP+ will target both managers and educators that are engaged with the children on a daily basis. Previous research has recommended this multi-level approach, with training to support policy and cultural change for managers and opportunities for professional development for educators [24]. Including multiple levels of staff within an organisation is an important factor in successful implementation strategies [33].

ATP+ is guided by Warrick’s (2009) change framework, aiding managers and educators in adopting and sustaining recommendedimplementation strategies related to the AP standards. ATP+ is a skill-building professional development course that provides resources and tools, including template forms, assignments with feedback, and ongoing virtual support through contact with a community of early years practitioners. Establishing ECEC-level policies to guide the use of implementation strategies for enhancing the implementation of the AP standards is a crucial initial step, although it is insufficient by itself [34,35]. Therefore, ATP+ enhances the Appetite to Play initiative capacity-building framework with additional training and resources to support application of set of facility-level implementation strategies that enhance continuous planning, monitoring and self-evaluation, while facilitating the institutionalization of AP standards for sustained implementation [36].

Educators assigned to the intervention group will gain access to the ATP+ content through an app called Pathverse. Pathverse is a no-code app builder platform that supports mobile-health (mHealth) research [37]. The Pathverse platform consists of a web portal for researchers to create engaging mHealth interventions with “drag and drop” features instead of coding. The content is then instantly displayed on the Pathverse mobile app accessible to research participants. This app was chosen due to the user-friendly method of creating content and functionality from a research perspective. Pathverse will host information for both educators and managers, which takes approximately 30 minutes to review over three weeks (see Fig 3).

**Fig 3 pone.0329276.g003:**
[figure not shown]
mHealth features of the ATP+ intervention in Pathverse.

### ATP+ intervention

ATP+ includes three interactive e-learning training modules that integrate strategies for implementing the AP Standards and sustaining its implementation. Table 1 summarized the key strategies implemented and sustainability strategies that are integrated in ATP+ using Powell et al.’s [38] taxonomy. Briefly, the three e-learning modules:

**Table 1 pone.0329276.t001:** Description of ATP+ components with a list of implementation and sustainability strategies that are used.

ATP+ Component	Goals	Target M = Manager, C = Champion, E = Educator	Strategy (Powell et al, 2015)
**Week 1 Module: Let’s get started**			
Interactive e-learning	Refresh your knowledge about active play (AP), Fundamental Movement Skills (FMS), and physical literacy, and learn the best practices for AP and how they can be used to meet the BC Director of Licensing guidelines.	M/C/E	Distribute educational materials
Interactive e-learning	Understand your role in promoting the use of best practices for AP and ensuring their sustained implementation.	M/C/E	Revise professional roles
Interactive e-learning	Use the AP Standards Self-Assessment Tool to examine whether you and your facility are following best practices for AP.	M/C/E	Audit and provide feedback
Interactive e-learning	Prepare for change by setting goal(s) (i.e., observe children’s AP or outdoor time activities; create more AP opportunities; use the Activity Planner on the Appetite to Play website to select FMS; organize space and equipment).	E	Distribute educational materials Capture and share local knowledge
Build community of practice	Start implementing AP best practices by developing a weekly schedule that aligns with these guidelines.	M/C	Stage implementation scale up Create a learning collaborative
Interactive e-learning	Prepare for change by enlisting a champion to support implementation and establish processes to sustain it.	M/C	Identify and prepare champion
Build community of practice	Prepare for change by settings goal(s) (i.e., do an inventory of resources, policies and practices; review your current practices and seek input on what needs to be changed; ensure the weekly schedule and/or AP planning includes FMS-promoting activities).	M/C with input from E	Stage implementation scale up Capture and share knowledge Create a learning collaborative Conduct local consensus discussions
**Week 2 Module: Making changes**			
Interactive e-learning	Refresh your understanding of why coordination-focused FMS are essential, learn new coordination activities and adapt them to promote engagement and physical literacy, and discover how to create new invitations for AP by designing installations or adding equipment/loose parts.	M/C/E	Distribute AP educational materials
Build community of practice	Tailor goals for making change (i.e., try out 3 FMS coordination skills adapting them for various abilities and sharing your insights; create a new installation to invite coordination-focused AP and evaluate its effectiveness; revise your daily practices to align with these changes).	E	Change physical structure and equipment Capture and share knowledge
Interactive e-learning	Become familiar with implementation support strategies.	M/C	Distribute educational materials
Interactive e-learning	Use the self-assessment tool to evaluate whether your facility has processes in place to implement and sustain change.	M/C	Audit and provide feedback
Interactive e-learning	Learn strategies that facilitate implementation and establish processes that ensure its sustainability.	M/C	Distribute educational materials
Build community of practice	Tailor goals for making changes (i.e., adjust the weekly schedule to include coordination and locomotor activities; brainstorm ideas for excursions and outdoor time; encourage your staff to share their installation ideas).	M/C with input from E	Stage implementation scale up Conduct cyclical small tests of change Capture and share knowledge Conduct local consensus discussions
**Week 3 Module 3: Maintaining Changes**			
Interactive e-learning	Refresh your understanding of why locomotor FMS are essential, explore new locomotor activities to sharpen skills, and utilize a list of questions designed to support children’s abilities.	M/C/E	Distribute educational materials
Build community of practice	Tailor goals for maintaining change (i.e., try 3 FMS locomotor skills adapting them for various abilities and sharing your insights; create a new installation to invite locomotor-focused AP and evaluate its effectiveness; revise your daily practices to align with these changes).	E	Stage implementation scale up Change physical structure and equipment Capture and share knowledge
Interactive e-learning	Learn to develop processes that support implementation and sustain it over time.	M/C	Distribute educational materials
Build community of practice	Tailor goals for maintaining changes (i.e., use the monitoring tool and debrief with your staff to identify barriers and facilitators to implementation, as well as potential solutions to enhance compliance with AP standards).	M/C with input from E	Audit and provide feedback Purposely re-examine the implementation Stage implementation scale up Assess for readiness and identify barriers and facilitators
**Post-Module Support (weeks 1–52) and Recognition**			
Push notifications	Reminder of tasks for making and maintaining changes as well as reminder to use the self-assessment and evaluation tools. Each notification includes a FMS activity and tasks specific to role. Weekly notifications start week 1 until week 52.	M/C/E	Remind
Professional development	Professional development credits provided as an incentive for completing the ATP+ training.	M/C/E	Incentive

Distribute educational materials to shape knowledge about: 1) why FMS are important; 2) what is AP and how can it support FMS development; 3) best practices for the implementation of AP Standards; 4) best strategies to support and sustain implementation.Provide audit and feedback tools to evaluate implementation of the best practices for AP and use of best strategies for sustaining the implementation of the AP standards.Support facilities in developing a formal implementation and sustainment plan (i.e., goal setting, timeframe & milestones, monitoring & discussion of progress) that promotes adaptability and stage the implementation of the AP Standards.Implement tools for monitoring the implementation of the AP standards as well as develop and organize a monitoring system for sustaining implementation.Identify and prepare champions (an individual within the organization who is enthusiastic and ready to support change) andestablish roles of managers, champions, and educators for the implementation and sustainment of the AP standards, ensuring everyone has a supportive and active role in both implementation and sustainment.

Two versions of the ATP+ program were created, tailored to the participant’s role at the facility (manager vs educator). While both programs have the same overall purpose and content, the strategies, tips and goals suggested are complimentary and focus on each participant’s specific role. In both versions of the ATP+ program, the content is separated into three distinct modules (see Table 1). Module 1 (“*Let’s get started*”) focuses on refreshing knowledge about AP, FMS, physical literacy, and the BC Director of Licensing AP Standards; learning best practices for AP, understanding roles of managers, champions, and educators in supporting AP; finding whether centres are using the best practices for AP; and starting to make changes with managers, champions, and educators aiming for different but complementary goals to align with their respective roles.

Module 2 (“*Making Changes*”) provides deeper learning related to teaching FMS with a particular focus on object-control/manipulation activities. It introduces new object-control/manipulation FMS activities, ways to adapt them for children with different abilities, and ideas to create invitations for AP. In Module 2, managers and champions learn the strategies for supporting implementation and how to maintain change over time. Both managers and champions assess whether they implement these support strategies and are provided with an action and communication plan for implementing the AP standards. At the end of the module, managers, champions, and educators plan to make changes by selecting goals that align with their roles.

Finally, Module 3 (“*Maintaining changes*”) focuses on expanding managers’ and educators’ learning about locomotor FMS and suggests new activities to promote these skills, along with ways to adapt these activities to suit the needs of 2.5-5.9-year-old children. In addition, managers and champions focus on specific tasks to integrate into schedules and routines to continue using the recommended implementation support strategies to support the AP standards. This module includes tools for monitoring and evaluation. The content differs for educators and managers/champions to better support each role.

The implementation of ATP+ is reinforced via push notifications. These are sent through thePathverse app and aim to: 1) develop and distribute AP materials and resources (e.g., tool box of ideas, resources for identifying new ideas, tools for planning AP activities); 2) remind all actors (managers, champions, and educators) about their roles and the actions they must initiate to implement the AP Standards and support its continued implementation; and 3) make the implementation and processes to sustain implementation dynamic and cyclical. Push notifications are initiated in week 1 and released weekly for a full year. The main purpose of these notifications is to provide ongoing support so the processes can all be restarted yearly with adaptation made possible. Implementation is also facilitated by building a community of practice within each centre to capture and share knowledge about implementation of the AP Standards and sustainment of the AP Standards over time.

In addition, all resources including the training materials, videos and links to external websites remain available in the Pathverse app for the duration of the study and beyond. Upon completion of the program, participants receive three professional development credit hours. Professional development hours are required for Early Childhood Educators to maintain their certification.

